## 3.0 STUDY DESIGN

Overview

A5225/HiFLAC is a randomized, open-label phase I/II dose escalation and validation study of the safety, tolerability, and therapeutic effect of an induction-consolidation strategy of high-dose fluconazole alone for the treatment of CM in HIV-infected participants. Comparison of this study’s results with historical data may be problematic and estimates of the performance of this drug for treatment of CM in resource-limited settings are very limited. For these reasons, a cohort treated with an ampho B-based regimen will be included in this study.

Stages, Steps, and Cohorts

Stages

The study will proceed in two stages. In Stage 1, Dose Escalation, up to three induction doses of fluconazole will be tested in sequentially enrolled cohorts. In Stage 2, Dose Validation, induction doses of fluconazole that were found to be safe in Stage 1 will be tested in simultaneously enrolled cohorts **along side 1 cohort that will receive high dose fluconazole plus 5FC**. In both Stage 1 and Stage 2, randomization to a cohort in which an ampho B-based regimen is administered in the induction phase will be included.

Steps

Within each stage, there will be multiple treatment steps for each cohort. For participants randomized to receive fluconazole only **or fluconazole plus 5FC**, the steps will be induction (Step 1), consolidation (Step 3), and maintenance (Step 4). For participants randomized to receive an ampho B-based induction regimen, the possible treatment steps will be induction (Step 1), induction following ampho B intolerance (Step 2), consolidation (Step 3), and maintenance (Step 4). Treatment within each step is described in section 5.1.

Cohorts

At study entry, participants will be randomized to one of at least 2 and at most 4 cohorts. The number of cohorts that are enrolling at any one time will depend on which stage of the study is open. Descriptions of the possible cohorts are presented in section 5.1

Stage 1 (Dose Escalation) Cohorts

Within Stage 1, a single fluconazole cohort and a single ampho B-based cohort will be open to enrollment at any one time. Participants will be randomized at Step 1 entry to receive a high dose of fluconazole for 4-10 weeks, or to receive the SoC dose of an ampho B-based regimen for approximately 2 weeks followed by fluconazole. The composition of the ampho B-based regimen will be determined by local SoC, but will include 0.7-1.0 mg/kg daily ampho B. The length of ampho B treatment will be determined in part by participants’ tolerance to the regimen. The total amount of ampho B that is administered to a participant in Step 1 is expected to be at least 8.4 mg/kg.

Opening of fluconazole cohorts at increasingly higher induction doses of fluconazole (ie, escalation of the fluconazole induction dose) will occur only after all available safety data, including, at a minimum, all data through day 14 for the last participant enrolled in the current cohort, have been reported and reviewed. Doses will not be escalated within any cohort. Dose escalation of fluconazole will stop at 2000 mg daily or earlier if the MTD is identified.

When either the MTD of fluconazole is reached or the week 10 visit for the final participant who entered the 2000 mg/day cohort is completed, all data through week 10 on all participants will be reviewed before Stage 2 of the study will be opened (see below).

Stage 2 (Dose Validation)

In Stage 2 (Dose Validation), participants will be randomized to receive an induction treatment of either an ampho B-based regimen or one of several doses of fluconazole at or below the MTD identified in Stage 1 **or to a dose of fluconazole that is at or below the MTD plus 5FC**. Before Stage 2 is opened, the protocol will be amended so that the specific dose or doses of fluconazole that will be tested in Stage 2 can be identified.

Stage 1 and Stage 2 Evaluations

Participants will be monitored for safety and toxicity throughout the study period.

The primary efficacy outcome measure is the change in quantitative CSF culture for cryptococcus. During screening or at entry, CSF samples for culture will be collected from all participants. At week 2, CSF samples will again be collected from all participants and will be cultured. Additional CSF samples will be collected and cultured at weeks 4, 6, 8, and 10, until a negative culture following 2 weeks of incubation is obtained. Treatment failure for any participant is defined as a week 10 CSF culture (which is read by or at week 12) that is positive for *C. neoformans*.

If a week 10 CSF culture is positive (by or at week 12), participants may discontinue study treatment and be treated according to local standard practice, at the discretion of the site investigator. Participants who discontinue study treatment prematurely should be encouraged to remain on study, off study treatment and should be encouraged to return for the week 24 visit.

PK samples will be obtained at specified time points from all participants enrolled in fluconazole induction cohorts (see section 10.0 for sampling information). Plasma, urine, serum, and CSF samples will be collected from all participants and stored for retrospective evaluation of novel diagnostic methodologies (collection schedule is presented in section 6.1).

## 4.0 SELECTION AND ENROLLMENT OF PARTICIPANTS

NOTE: Inclusion and exclusion criteria listed below apply to both Stage 1 and Stage 2 of the study.

### 4.1 Inclusion Criteria – Step 1

- - 1. Cryptococcal meningitis documented either by a positive CSF cryptococcal culture, a positive CSF India ink preparation, or a positive CSF cryptococcal antigen latex agglutination test within 7 days prior to entry.

**NOTE: Patients may be enrolled into the study with a cryptococcal meningitis (CM) infection that is documented solely by a test result from a referring laboratory (ie, not the site’s DAIDS-approved laboratory). However, CM must be confirmed by Day 5 at a laboratory that is participating in EQA (eg, the site laboratory that has received approval from the ACTG to conduct A5225). Treatment must not be delayed while awaiting confirmation of the screening test result.**

- - 1. CSF collection for quantitative cryptococcal culture within 72 hours prior to study entry or planned to be performed at study entry.

4.1.3 HIV-1 infection, documented by any licensed rapid HIV test or HIV enzyme or chemiluminescence immunoassay (E/CIA) test kit at any time prior to study entry and confirmed by or within 10 days after study entry by a licensed Western blot or a second antibody test by a method other than the initial rapid HIV and/or E/CIA, or by HIV-1 antigen, plasma HIV-1 RNA viral load.

NOTE: The term ‘licensed’ refers to an FDA-approved kit which is required for all IND studies. For non-US sites, ‘licensed’ refers to a kit that has been certified or licensed by an oversight body within that country and that has been validated internally. However, non-US sites are encouraged to use FDA-approved methods for IND studies.

The World Health Organization and the US Centers for Disease Control and Prevention guidelines mandate that confirmation of the initial test result must use a test that is different from the one used for the initial assessment. A reactive initial rapid test should be confirmed by either another type of rapid assay or an E/CIA that is based on a different antigen preparation and/or different test principle (eg, indirect versus competitive), or a Western blot or a plasma HIV-1 RNA viral load.

- - 1. Men and womenage  16 years.

4.1.5 Ability to take oral medications.

NOTE: Administration of fluconazole tablets via nasogastric tube is permitted.

4.1.6 For patients with a co-morbid complication of HIV, including opportunistic infections, **ability to monitor treatment efficacy (CSF sampling) and toxicity management of study drugs**, as judged by the site investigator.

NOTE: **CSF sampling may not be possible or safe in the setting of CNS mass lesions. Such participants should be entered and continued in study only in consultation with neurosurgery/neuroradiology after assessment of the safety of CSF sampling.**

4.1.7 For female participants of reproductive potential (defined as girls who have reached menarche or women who have not been post-menopausal for at least 24 consecutive months, ie, who have had menses within the preceding 24 months, or have not undergone surgical sterilization [eg, hysterectomy, or bilateral oophorectomy or salpingotomy]) a negative serum or urine pregnancy test result must be obtained within 2 days prior to study entry.

4.1.8 All participants must agree not to participate in the conception process (eg, active attempt to become pregnant or to impregnate, sperm donation, in vitro fertilization).

4.1.9 If participating in sexual activity that could lead to pregnancy, female study participants must agree to the simultaneous use of two forms of contraceptive (from the list below) during such sexual activity, and male study participants must agree to use a condom during such sexual activity. This requirement continues while the study participant is on study treatment and for 6 weeks after fluconazole has been discontinued.

- Condoms (male or female) with or without a spermicidal agent
- Diaphragm or cervical cap with spermicide
- IUD (intrauterine device)
- Injectable DepoProvera
- Tubal ligation

NOTE: Use of oral hormone-based contraceptives is prohibited while a study participant is taking any study-provided fluconazole.

4.1.10 Study participants who are not of reproductive potential (defined as women who have been post-menopausal for at least 24 consecutive months, or women who have undergone surgical sterilization [eg, hysterectomy, or bilateral oophorectomy or salpingectomy], or men who have documented azoospermia), are eligible without the requirement to use contraceptives.

NOTE: Lack of reproductive potential requires written documentation or oral communication from a clinician or clinician’s staff documented in source documents.

4.1.11 Willingness and ability to adhere to dose schedules and mandatory procedures.

4.1.12 Measured or calculated creatinine clearance of ≥50 mL/min within 3 days prior to study entry.

A calculator is available at the Data Management Center at [*https://www.fstrf.org/ACTG/*](https://www.fstrf.org/ACTG/) or at [*http://www.fstrf.org/ACTG/index.html*](http://www.fstrf.org/ACTG/index.html).

4.1.13 The following laboratory values within 3 days prior to study entry:

- aspartate aminotransferase (AST), alanine aminotransferase (ALT), and alkaline phosphatase ≤ 5 X the upper limit of normal (ULN)
- total bilirubin ≤ 2.5 X ULN
- absolute neutrophil count (ANC) ≥ 750/mm3
- platelet count ≥ 50,000/mm3
- hemoglobin  7.0 g/dL

4.1.14 Ability and willingness of the participant or legal guardian/representative to give informed consent.

4.1.15 Availability at the site of at least 2 weeks of its standard of care ampho B-based regimen.

### 4.2 Exclusion Criteria - Step 1

4.2.1 Expected survival of ≤ 2 weeks, in the opinion of the site investigator and, if available, the primary care provider.

4.2.2 For patients with a co-morbid complication of HIV, anticipated difficulty, in the opinion of the site investigator, in judging response to study treatment as a result of the co-morbid complication or the drugs used to treat it.

4.2.3 Breastfeeding.

4.2.4 A prior episode of CM, either as indicated by patient or as noted in patient medical records.

4.2.5 Use of any of the following drugs, within the time periods described:

- warfarin within 3 days prior to study entry
- terfenadine or cisapride within 24 hours prior to study entry
- other drugs known to interact with fluconazole, the co-administration of which may lead to life-threatening side effects, within 10 days prior to study entry (see section 3 of the current A5225/HiFLAC MOPS)
- drugs that may decrease the effect of fluconazole, or whose co-administration may increase their own toxicity or decrease their own efficacy, within 24 hours prior to study entry (see section 3 of the current A5225/HiFLAC MOPS)
- phenytoin, carbamazepine, cyclosporin A, tacrolimus, sirolimus, astemizole, or long-acting barbiturates within 7 days prior to study entry
- more than 72 cumulative hours of systemic treatment **thought to be effective in the management of cryptococcal meningitis** with **fluconazole at >400 mg/day or itraconazole > 200 mg/day or amphotericin B >0.3 mg/kg/day or liposomal amphotericin B >0.3 mg/kg.day or flucytosine >25 mg/kg/day** for any reason within 14 days prior to study entry.

4.2.**6** Known allergy, sensitivity to, or intolerance of fluconazole or other imidazole or triazole compounds, or to ampho B or other components of the standard of care ampho-B based regimen.

4.2.**7** History of clinically significant cardiac disease, in opinion of site investigator, including symptoms of ischemia, coronary artery disease, congestive heart failure, or arrhythmia.

4.2.**8** ECG (electrocardiogram) with QTc interval greater than 450 msec within 7 days prior to study entry.

4.2.**9** History of CNS disorder (excluding mood disorders) or concurrent CNS disorder(s) that, in the opinion of the investigator, would interfere with assessment of efficacy (e.g., ability to perform CSF sampling) such as lymphoma, neurocysticercosis, or toxoplasmosis.

4.2.**10** Receipt of investigational drug therapy within 30 days prior to study entry without prior approval of the A5225/HiFLAC core team.

4.2.1**1** Active drug or alcohol use, dependence, or other conditions that in the opinion of the site investigator would jeopardize the safety of a participant in the study or would render the person unable to comply with the study plan.

### 4.3 Inclusion Criteria – Step 2

4.3.1 Randomization to an ampho B-based regimen in Step 1.

4.3.2 Receipt of at least one dose of ampho B-based regimen in Step 1.

4.3.3 Premature discontinuation of ampho B in response to the occurrence of any treatment-limiting toxicity, as described in section 5 of the A5225/HiFLAC MOPS.

### 4.4 Exclusion Criteria – Step 2

4.4.1 Receipt of fluconazole monotherapy in Step 1.

4.4.2 Receipt of ≥8.4 mg/kg ampho B.

4.4.3 At or beyond Day 17 in Step 1.

### 4.5 Inclusion Criteria - Step 3

4.5.1 For participants in Step 1 who are currently receiving study-provided fluconazole, with no plans to discontinue study treatment, a negative CSF culture after 2 weeks incubation from a sample obtained at or before week 6 (days 35-49).

4.5.2 For participants in Step 1 who are currently receiving an ampho B-based regimen or alternative treatment, completion of approximately 2 weeks of treatment.

NOTE: The total amount of ampho B received by a participant is expected to be approximately 8.4 mg/kg.

4.5.3 For participants in Step 2 who are currently receiving study-provided fluconazole, with no plans to discontinue study treatment, negative CSF culture after 2 weeks incubation from a sample obtained at or before week 6 (day 35-49).

### 4.6 Exclusion Criteria – Step 3

4.6.1 On study treatment beyond week 10 (day 77) in Step 1 or Step 2.

4.6.2 Currently off study treatment.

### 4.7 Inclusion Criterion – Step 4

4.7.1 On study treatment at week 10 (day 63-77), with no plans to discontinue study treatment.

### 4.8 Exclusion Criterion – Step 4

4.8.1 Currently off study treatment.

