# SCHEMA

A5225/HiFLAC

A Phase I/II Dose-Finding Study of High-Dose Fluconazole Treatment in AIDS-Associated Cryptococcal Meningitis

DESIGN Overview

A5225/HiFLAC is a phase I/II dose escalation and validation study of the safety, tolerability, and therapeutic effect of an induction-consolidation strategy of high-dose fluconazole alone **or with oral flucytosine (5FC)** for the treatment of cryptococcal meningitis (CM) in HIV-infected participants. As noted in section 2.2, comparison of this study’s results with historical data may be problematic. For this reason, a cohort treated with amphotericin B deoxycholate (which will be referred to as ‘ampho B’ in this study) alone or in combination with 5-fluorocytosine **or fluconazole, according to local standard of care** (**any** of which will be referred to as ‘an ampho B-based regimen’ in this document) will be included in this study.

The study will proceed in two stages (see A5225/HiFLAC Stages 1 & 2 Flow Chart). In Stage 1, Dose Escalation, up to three induction doses of fluconazole **alone** will be tested in sequentially enrolled cohorts. Stage 2, Dose Validation, will not open until the maximum tolerated dose (MTD) of fluconazole has been identified in Stage 1. In Stage 2, induction doses of fluconazole that are found to be safe in Stage 1 will be tested in simultaneously enrolled cohorts. In each stage, participants will be randomized at entry into Step 1. Over the course of the study, participants will register to subsequent steps (Steps 2-4) based on their initial randomization and/or their response to treatment. The study steps are:

- Step 1: Induction therapy with either high dose fluconazole or ampho B
- Step 2: Induction following early ampho B intolerance (only for participants randomized to ampho B treatment in Step 1) (fluconazole at 400-800 mg daily)
- Step 3: Consolidation therapy (fluconazole 400 mg daily)
- Step 4: Maintenance therapy (fluconazole 200 mg daily)

Stage 1 (Dose Escalation)

Stage 1 will include up to three sequentially enrolled cohort sets, each testing a different induction dose of fluconazole and gathering data about ampho B-based treatment (see A5225/HiFLAC Stage 1 Flow Charts #1-3). Each cohort will enroll up to 24 participants randomized to fluconazole and up to 8 participants randomized to an ampho B-based regimen. At any time during the study, enrollment may be halted for safety reasons.

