### 6.2 Timing of Evaluations

6.2.1 Pre-Enrollment Evaluations

Screening

Screening evaluations to determine eligibility must be completed within 3 days prior to study entry unless otherwise specified. Entry may take place on the same day as screening if all required information is available and acceptable.In the event of a delay in entry into study beyond 24 hours, **800**mg FCZ daily for a maximum of 3 days or total dose of **2400**mg is permissible.

The ACTG Screening Failure Results Form must be completed for any patient who is screened for this study but who does not enroll into it.

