6.2.2 On-Study Evaluations

Entry

On-study evaluations are performed only after a participant is enrolled into the study. However, the following evaluations do not need to be repeated at entry if performed within 72 hours prior to entry: CD4 cell count, plasma HIV-1 RNA, LP with opening pressure recorded, CSF cryptococcal antigen test, CSF cultures initiated (quantitative and qualitative), CSF analyses, and stored CSF sample. Storage of a cryptococcal isolate from CSF collected at screening or entry is sufficient.

Participants must begin study-assigned treatment within 72 hours after entry, however, initiation of study-assigned treatment within 24 hours after entry is strongly encouraged.

Post- Entry

The visit schedule through day 7 should be based on the first day of treatment (day 1 = first day after first dose of fluconazole or ampho B-based regimen), not solely on the date of enrollment. The visits listed for Days 4 through 7 should be completed ± 1 day of those time points as indicated in the SoE, section 6.1.2 and 6.1.3.

The week 2 visit should occur on day 14, but may be completed 12-17 days after initiation of study treatment.

The weeks 4-10 visits should occur on the week noted in the SoE, but may be completed ± 3 days as indicated in the SoE, sections 6.1.2 and 6.1.3. The week 24 visit may be completed ±7 days of that week, as indicated in sections 6.1.2 and 6.1.3. Note that for participants whose previous CSF culture was positive, at least 14 days must elapse between visits.

Step 1 (Induction)

Participants are expected to remain on Step 1 from 2 to 10 weeks depending on the treatment to which they are randomized and their response to that treatment. Participants randomized to ampho B will register to Step 3 after approximately 2 weeks of ampho B treatment. Some participants taking ampho B may register to Step 2 (see below) before entering Step 3.

Participants randomized to fluconazole will remain in Step 1 until week 10 or until a CSF culture is negative, whichever is earlier.

Step 2 (Induction Following Amphotericin B Deoxycholate Intolerance)

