6.2.4 Premature Treatment or Study Discontinuation

Confirmatory HIV Test/Qualifying CSF culture

If **any of the following is true in the given time frame, then** the participant will be discontinued from study treatment, followed for up to 2 weeks, and then discontinued from the study**:**

- the confirmatory HIV test is negative
- the qualifying CSF culture is negative after 2 weeks of incubation
- **a confirmatory CSF antigen titer is negative by Day 5 AND no positive result from the qualifying CSF culture is obtained through Day 4**
- a study entry quantitative culture was required but not performed

In such cases, the participant will be treated as deemed appropriate by his/her primary physician. These participants should complete the evaluations in the Premature Treatment or Study Discontinuation column in the SoE at the time of treatment discontinuation and again approximately 2 weeks later, for study discontinuation; no fluconazole trough PK sample should be collected at these participants’ study discontinuation visit.

Premature Treatment Discontinuation

All participants who prematurely discontinue study treatment (see section 8.1) at any time during the study should complete the Premature Treatment or Study Discontinuation evaluations (per the SoE) within one week after treatment discontinuation. With the exception of participants randomized to ampho B who prematurely discontinue ampho B in Step 1 and who are eligible to register to Step 2, participants who prematurely discontinue study treatment will remain on the step they are on at the time of treatment discontinuation (without registering to subsequent steps) and will continue to be followed on study, off treatment per the SoE, except as noted in sections 6.3.22 and 6.3.24.

Premature Study Discontinuation

Participants who discontinue the study prematurely (see section 8.2) should complete the Premature Treatment or Study Discontinuation evaluations (per the SOE) at the time of study discontinuation.

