**A negative screening CSF culture is defined as**

- **a negative culture after 2 weeks of incubation even in the setting where the CSF antigen testing is positive by latex agglutination from a referring laboratory**

**or**

- **a negative culture after 5 days of incubation if there is no yeast found on culture and there is a negative CSF antigen test by the latex agglutination method by Day 5 from an approved laboratory.**.
- Failure to obtain a quantitative CSF culture at screening or entry.
- Failure to initiate study treatment within 72 hours after entry.
- Initiation of NVP prior to fluconazole dose reduction to ≤ 400 mg daily
- Request of the primary care provider if s/he thinks the study is no longer in the best interest of the participant.
- Failure by the participant to attend three consecutive clinic visits.
- Request by the participant to withdraw.
- Participant judged by the investigator to be at significant risk of failing to comply with the provisions of the protocol as to cause harm to self or seriously interfere with the validity of the study results.
- At the discretion of the Office for Human Research Protections (OHRP), Food and Drug Administration (FDA), NIAID, ACTG [including the Study Monitoring Committee (SMC)], local IRB/EC or other regulatory authority, industry supporter, or investigator.

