Stage 1 can provide preliminary guidance on efficacy for the choice of cohorts to move to Stage 2. With 20-22 subjects with evaluable quantitative culture results over time per group, a difference in mean change in Cryptococcus (expressed as log10 CFU/ml CSF/day) of about 80% of the standard deviation of the measure can be detected with 90% power using a relaxed one-sided 0.10 alpha-level test. For example, if EFA (early fungicidal activity defined as the change from day 0 to day 14) is -0.30 with a standard deviation (s.d.) of 0.15 log10 CFU/ml CSF/day, an increase in the clearance to about -0.42 can be detected.

We recognize that the many neurological complications of CM may obscure drug-related ones. We will monitor participants for unusual neurological manifestations of CM that might be attributed to fluconazole. With 20 (22) evaluable participants, there is a 64% (68%) chance of seeing at least one episode of a completely unexpected unacceptable event that has a true underlying rate of occurrence of 5%. Should we see one or more DLTs associated with cardiac toxicity at a dose level, a targeted review will be triggered. This will happen with 88% probability if the underlying rate of cardiac toxicity is 10%. Should we see 2 or 3 DLTs in 20-22 participants at a dose level, and 2 of 2 or 2-3 of 3 are associated with hepatic toxicity, a targeted review will be performed before the dose can be escalated to the next level. As noted in 9.3.2, the nature and rates of all events will be evaluated prior to accepting any dose for further testing in Stage 2.

9.3.2 Stage 2

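### Baseline quantitative CSF may be collected only after open-label randomisation, with removal from the study if it is missed, and its timing is not tied to the first study dose

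*Protocol*

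**What the plan says.** **Baseline sample and allocation.** Section 4.1.2 requires "CSF collection for quantitative cryptococcal culture within 72 hours prior to study entry or planned to be performed at study entry". The Schema states: "In each stage, participants will be randomized at entry into Step 1". Section 3.0 describes the trial as open-label. Section 6.2.2 places on-study evaluations after enrolment and waives the entry LP only where one was done in the preceding 72 hours.

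**Missing baseline.** Section 6.2.4 lists "a study entry quantitative culture was required but not performed" among the reasons for stopping study treatment and, after no more than two weeks of follow-up, leaving the study. Section 8.2 repeats it: "Failure to obtain a quantitative CSF culture at screening or entry".

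**Timing.** Section 6.2.2 says "Participants must begin study-assigned treatment within 72 hours after entry" and urges a start within 24 hours. It counts the week 2 visit from the first dose: day 14, with days 12 to 17 allowed. Section 4.2.5 excludes only "more than 72 cumulative hours of systemic treatment" above listed dose thresholds in the 14 days before entry. Section 6.2.1 allows bridging fluconazole when entry is delayed beyond 24 hours, capped by duration and amount ("FCZ daily for a maximum of 3 days or total dose of" a stated figure). Section 9.3.1, in a power example, describes EFA as "early fungicidal activity defined as the change from day 0 to day 14".

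**The concern.** Whether a baseline culture exists should be settled before allocation. Here it can be settled afterwards, by staff and participants who know the arm, and a missed sample ends both treatment and follow-up. Survival is a primary outcome (9.2.1.3) and 10-week survival is a hypothesis (1.1.2.2), so the loss goes beyond the culture endpoint.

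The second issue is what the week 2 change measures. The week 2 clock starts at the first study dose, but the baseline clock does not. The interval between the two cultures can therefore include days without treatment, or days on drugs other than the assigned one. Absolute EFA feeds the decision on whether high-dose fluconazole merits a further trial, so a baseline that floats relative to the first dose weakens that evidence.

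**Working it through.** **1. Order of events when the LP is only planned.** Eligibility met (4.1.2); open-label randomisation at entry (Schema, 3.0); entry LP among the on-study evaluations (6.2.2); culture not performed; off treatment, then off study (6.2.4, 8.2). Nothing in this chain requires the LP before allocation, and no text expressly places an entry LP before the first dose. The Stage 1 replacement rule in 9.1 does not name a culture that was not performed, although its category of lacking a positive entry culture might be stretched to cover it. One such loss is 1/8 = 12.5% of a Stage 1 ampho B cohort and 1/24 = 4.2% of a fluconazole cohort.

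**2. The plan's own power figure (9.3.2).** Inputs: difference 0.10 and SD 0.15 log10 CFU/ml CSF/day, 48 per arm, two-sided 0.05. Power = Φ(δ / (σ√(2/n)) − 1.96) = Φ(0.10/0.0306 − 1.96) = Φ(1.31) = 90.4% (89.8% by t-test). The stated 90% reproduces. If losses left 46, 43 or 38 per arm (assumed 4%, 10% or 21%), power would be 89%, 87% or 83%.

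**3. Lead time.** Maximum from baseline LP to first study dose: 72 h + 72 h = 6 days. Interval between cultures: 12 days (LP at first dose, week 2 visit on day 12) to 17 + 3 + 3 = 23 days. Both ends stack the permitted limits.

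**4. Effect on one participant's EFA**, with a true rate of −0.30 per day (9.3.1) and the week 2 LP on day 14:
- Six untreated lead days, divided by actual days: −0.30 × 14/20 = −0.21, an error of 0.09.
- 72 h of ampho B falling wholly between the LP and the first dose, at the 0.31 log10/day tabulated for ampho B alone in 2.1.2: 0.31 × 3 = 0.93 log10. Spread over a nominal 14 days this is 0.066 per day. It is a single worst-case participant, and it depends on the nominal divisor. Over the actual 17 days the same case reads (0.93 + 4.20)/17 = 0.302, almost no error, because the two rates are nearly equal.

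**5. Effect on the arm comparison.** With lead assumed uniform over 0 to 6 days and the same in both arms, simulated power is about 88% and the mean difference shrinks from 0.10 to about 0.084 on actual days. If mean lead differed between arms by 1 or 2 days (assumed, with no clearance before dosing), the bias would be 0.30 − 0.30 × 14/15 = 0.020 or 0.30 − 0.30 × 14/16 = 0.0375. Against a standard error of 0.0306, the false-positive rate would be about 10% or 23% instead of 5%. The documents give no such difference; these figures show sensitivity only.

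**The case against.** It can fairly be said that 6 and 23 days are extremes: a start within 24 hours is urged and week 2 is aimed at day 14. The prior-treatment allowance and the bridging fluconazole both fall before entry, hence before randomisation, and balance on average between concurrent arms. Participants who cannot be sampled are largely screened out by 4.1.6, 4.1.11 and 4.2.9. The planned-LP limb also serves a purpose, since patients may enter on a referring laboratory's result. All of this stands, and it limits the size of the problem. It does not explain why collection should wait until after allocation.

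A reader might go further and divide the change by a fixed 14 days, then set the range across the day 12 to 17 window against the 0.10 design difference. The documents do not support this. The protocol expresses EFA as a daily rate and states no fixed divisor; the day 0 to 14 wording sits inside a power example, and a SAP may well use actual dates. The comparison would also set a range between individuals against a mean difference between arms. Even with a fixed divisor and visits uniform over the window, the added SD is 1.44 × 0.30/14 = 0.031. Total SD becomes about 0.153 and power remains about 89%.

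A reader might also infer that the sample size is wrong, or that pre-entry antifungals bias the randomised comparison. Neither follows.

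**Conclusion.** The concern holds in two parts of unequal weight. The firmer one is the exclusion after open-label allocation for a missing baseline culture. The text establishes it, it affects survival as well as EFA, and an unseen SAP could not recover follow-up that the protocol ends. Its frequency is unknown, so no bias can be computed.

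The second is that baseline is not anchored to the start of study treatment: up to 6 days' lead in the extreme, with up to 72 h of effective antifungals allowed before entry. The stated power is not wrong and concurrent arms are balanced on average for pre-entry exposure. The exposed quantities are absolute EFA; comparisons between fluconazole doses, because Stage 1 doses were enrolled sequentially and 9.3.2 pools the stages for efficacy without adjustment; and any arm comparison in which the delay from entry to first dose differs. A differential delay is plausible, because ampho B is intravenous and locally sourced while fluconazole is study-supplied tablets, but no figure in the protocol shows one.

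**What to change.** **(a) Eligibility and removal.** In 4.1.2, require that CSF for quantitative culture has been collected before randomisation. Only collection is needed, not a result, so same-day entry remains possible. Reconcile 6.2.4 and 8.2 with this, and keep an explicit rule for CSF that was collected but not cultured. Keep every randomised and treated participant in follow-up for safety and survival; whether study treatment continues in such a case is a clinical decision not addressed here.

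**(b) EFA.** State it as log10 change per actual day between the two cultures. Use antifungal exposure before randomisation as a baseline covariate; section 6.3.3 already records start and stop dates, some of them estimated, so days rather than hours are realistic. Treat the delay and any non-assigned antifungal between entry and first dose only descriptively or in a sensitivity analysis by arm. These arise after allocation and should not be a primary covariate or a ground for exclusion. As section 6.3.5 exempts ampho B from its list of recorded antifungals, check that ampho B given to a fluconazole participant in that gap would be captured.

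**Cost and limits.** The changes are to wording; the LP is already mandatory and only moves ahead of randomisation, which may wait some hours for it. The change does not shorten the 72 h + 72 h windows, and removals for a negative culture or HIV test remain. Dividing by actual days still dilutes EFA when lead days are untreated, so lead time should be tabulated by arm. Section 5.1 describes Stage 1 as completed, so (a) can help only Stage 2, while (b) can serve the pooled analysis.
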